#### 9.4 GRADING AND RELATEDNESS OF ADVERSE EVENTS

##### 9.4.1 Grading of Severity of an Adverse Event

The severity of each adverse event will be graded as mild, moderate, severe, life threatening, or death which corresponds to Grades 1, 2, 3, 4 and 5, respectively on the National Cancer Institute Common Toxicity Criteria for Adverse Events (NCI CTCAE) version 3.0. These criteria must be used in grading the severity of adverse events. The criteria can be found at: [www.fda.gov/cder/cancer/toxicityframe.htm](http://www.fda.gov/cder/cancer/toxicityframe.htm).

For those adverse events which are not listed as part of the NCI CTC, the same grading system should be used, where:

**Grade 1:**        **Mild** corresponds to an event not resulting in disability or incapacity and which resolves without intervention;

**Grade 2:**        **Moderate** corresponds to an event not resulting in disability or incapacity but which requires intervention;

**Grade 3:**      **Severe** corresponds to an event resulting in temporary disability or incapacity and which requires intervention;

**Grade 4:**      **Life-threatening** corresponds to an event in which the patient was at risk of death at the time of the event;

**Grade 5:**      **Fatal** corresponds to an event that results in the death of the patient.

#### 9.4.2      Relatedness to Study Drug

The Investigator must attempt to determine if an adverse event is in some way related to the use of the study drug. This relationship should be described as follows:

1. Related:      The reaction follows a reasonably temporal sequence from administration of the drug and follows a known response pattern to a similar class of drugs.
2. Not Related: Concomitant illness, accident or event with no reasonable association with treatment, or the reaction has little or no temporal sequence from administration of the study drug, and/or a more likely alternative etiology exists.

If discernible at the time of completing an adverse event CRF, a specific disease or syndrome rather than individual associated signs and symptoms should be identified by the Investigator and recorded on the appropriate adverse event CRF. However, if an observed or reported sign, symptom, or clinically significant laboratory anomaly is not considered by the Investigator to be a component of a specific disease or syndrome, then it should be recorded as a separate adverse event on the appropriate CRF. (Clinically significant laboratory abnormalities are those that are identified as such by the Investigator and/or are those that require intervention).

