## 6. PATIENT SELECTION

### 6.1 NUMBER OF PATIENTS

Up to nine patients are expected to be enrolled.

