## *9.3 DOCUMENTING ADVERSE EVENTS*

The Investigator should elicit information regarding the occurrence of adverse events through open-ended questioning of the patient, physical examination and review of laboratory results.

All adverse events, whether serious or not, will be described in the source documents and the adverse event page of the case report form. All new events, as well as those that worsen in intensity or frequency relative to baseline, that occur after administration of study drug through the period of protocol-specified follow-up must be captured.

Information to be reported in the description of each adverse event includes but not limited to:

- Medical diagnosis of the event (if a medical diagnosis cannot be determined, a description of each sign or symptom characterizing the event should be recorded)
- The date of onset of the event
- The date of resolution of the event
- Whether the event is serious or not
- Action taken:
  - None
  - Change in the study drug administration (e.g., temporary interruption in dosing)
  - Drug treatment required (specify)
  - Non-drug treatment required (specify)
  - Hospitalization or prolongation of hospitalization required (complete SAE page)
  - Diagnostic procedure performed (specify)
  - Patient discontinued from the study (complete final visit section of the CRF)
- Outcome:
  - Event resolved
  - Event resolved with sequelae
  - Event ongoing
  - Patient died (notify Collectar immediately, complete the SAE page and final visit section of the CRF)
- Patient condition is related or not related to the study drug
- Patient's condition is intermittent or continuing
- The grade of the event based on the NCI common toxicity criteria

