### *10.2 DOSE LIMITING CRITERIA*

In general, Dose Limiting Toxicities (DLTs) will be considered as toxicities that are related to treatment with I-131-CLR1404 and that are:

1. Hematological
  - a. Any CTCAE Grade 4 toxicity (except Grade 4 neutropenia without concurrent fever which must be present for  $\geq 7$  days to constitute a DLT)
  - b. CTCAE Grade 3 neutropenia with fever
  - c. CTCAE Grade 3 thrombocytopenia associated with bleeding
2. Non-Hematological
  - a. Any CTCAE Grade 3 toxicity despite adequate supportive care (supportive care limited to nausea, vomiting and diarrhea only)
  - b. Any CTCAE Grade 4 toxicity

If 2 patients experience a DLT, study enrollment will be stopped pending discussions with the Principal Investigator, Collectar Medical Monitor and the Agency.

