#### *11.3 SAMPLE SIZE*

As there is little information on the effect of I-131-CLR1404, this study is meant to be hypothesis generating and no formal sample size calculation will be performed.

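### Section 9.4.2 makes class precedent a condition for 'Related' and leaves a gap between its two categories, so a well-timed new toxicity may go uncounted in the two-patient DLT stop

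*Protocol*

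**What the plan says.** Section 9.4.2 asks the investigator to decide whether an event is in some way related to the study drug, and then gives two categories. Related requires two things, joined by 'and': that the timing after administration is reasonable, and that the reaction "follows a known response pattern to a similar class of drugs". Not Related covers a concomitant illness, accident or event without reasonable association with treatment, or a case where "the reaction has little or no temporal sequence from administration of the study drug, and/or a more likely alternative etiology exists". There is no intermediate category, and 'similar class' is not defined.

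Section 9.3 asks for the same two-way answer: "Patient condition is related or not related to the study drug". No other section defines relatedness.

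Three other rules use the result:

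- Section 10.2: "Dose Limiting Toxicities (DLTs) will be considered as toxicities that are related to treatment with I-131-CLR1404" and that also meet the listed grades. "If 2 patients experience a DLT, study enrollment will be stopped pending discussions".
- Section 9.1.1: follow-up of an event may end at Day 42, except that drug-related events are followed to resolution.
- Sections 5.1 and 7.3: after 30 days, absence of drug-related toxicity is a condition for moving on to other, non-investigational therapy.

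On size, section 6.1 states: "Up to nine patients are expected to be enrolled".

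**The concern.** Requiring class precedent is an awkward test for a compound that section 2 calls novel, whose metabolism section 7.6 describes as only partly understood, and for which section 11.3 gives as the reason for having no sample size calculation: "As there is little information on the effect of I-131-CLR1404". Determining safety is a secondary objective. A reaction not previously seen with similar drugs is one of the things such a study should be able to register, and it is the kind of event that the second condition of Related shuts out.

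The two-patient DLT rule is the protocol's only numeric safety trigger. With a threshold of two and at most nine patients, the classification of one patient's event can decide whether the rule fires. Because the text does not say where a gap event belongs, sites (approximately four, section 5.2) may also classify the same event differently.

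**Working it through.** The protocol gives no DLT rate, power or stopping probability, so there is no planned figure to reproduce. The check has two parts.

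**1. The definitions side by side.** Take an event with plausible timing, no known precedent in a similar class, and no more likely alternative cause.

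| Test in 9.4.2 | Does this event meet it? |
|---|---|
| Related, condition 1: reasonable timing | Yes |
| Related, condition 2 (joined by 'and'): known class pattern | No |
| **Related overall** | **No** |
| Not Related: no reasonable association with treatment | Not evidently; the timing fits and nothing else explains the event |
| Not Related: little or no temporal sequence | No |
| Not Related: more likely alternative cause | No |
| **Not Related overall** | **Not met** |

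The text is therefore indeterminate for this event. Section 9.3 still requires one of the two answers. If the site takes the conditions for Related literally, the answer is 'not related', and the event drops out of the three rules listed above. An event with class precedent meets both conditions of Related and is not affected.

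**2. What this could do to the enrolment stop.** Inputs: n = 9 (6.1) and a threshold of 2 patients (10.2). Two further quantities are assumptions, because the documents give neither: p, the true per-patient rate of DLT-grade toxicity caused by the drug; and g, the share of that toxicity that lies in the gap and is recorded as not related. With independent patients and q = p(1 − g),

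P(at least 2 counted DLTs) = 1 − (1 − q)^9 − 9q(1 − q)^8.

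For p = 0.20:

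- g = 0, q = 0.20: 1 − 0.1342 − 0.3020 = 0.564
- g = 0.5, q = 0.10: 1 − 0.3874 − 0.3874 = 0.225
- g = 1, q = 0: 1 − 1 − 0 = 0

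| Assumed p | g = 0 | g = 0.5 | g = 1 |
|---|---|---|---|
| 10% | 0.225 | 0.071 | 0 |
| 20% | 0.564 | 0.225 | 0 |
| 30% | 0.804 | 0.401 | 0 |
| 40% | 0.929 | 0.564 | 0 |
| 50% | 0.980 | 0.700 | 0 |

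A stop spares an enrolment only if the second DLT falls within the first eight patients. With n = 8 in the same formula, the values at p = 20% are 0.497 (g = 0) and 0.187 (g = 0.5); at p = 30% they are 0.745 and 0.343.

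The column g = 0 also shows the rule once the gap is closed. The column g = 1 is an extreme: all the toxicity is without class precedent and every site reads the definition literally.

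**The case against.** The strongest objection is that the text does not push in one direction. A gap event fails Not Related as well, and the opening question in 9.4.2, whether the event is in some way related, invites an investigator to answer 'related'. This stands. A reader might infer that a new toxicity can never be a DLT, or that its chance of being counted is zero. The protocol does not support that, because nothing in it says that unclassified events default to Not Related. Zero arises only under the literal reading with g = 1.

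A reader might also infer that the safety summary is biased. That is not supported either. Section 11.5 reports adverse events for all infused patients without splitting them by relatedness, and 9.1.1 and 9.3 record all events whether related or not.

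Nor can it be assumed that most unexpected toxicities lack precedent. The sentence in 11.3 explains the absence of a sample size calculation; it does not say that class effects are unknown. Section 2 describes decades of use of radioactive isotopes against tumours and names marrow, liver and kidneys as organs to spare. Three of the five DLT criteria in 10.2 are haematological. If radiopharmaceuticals count as the similar class, marrow suppression has precedent and is counted.

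Finally, 10.2 opens with a general qualifier, does not cite 9.4.2, and leads to a pause for discussion. Other safeguards do not depend on relatedness: all SAEs go to the Medical Monitor within 24 hours and are evaluated (9.2), and the sponsor may discontinue for unacceptable toxicity (10.3). These limit the harm. They do not replace the DLT count, since 10.2 offers no other meaning of related and the sponsor's discretion has no numeric trigger.

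**Conclusion.** The point holds as a defect in a stated definition. Class precedent is a necessary condition for Related, the class is undefined, and the two categories are not exhaustive. On a literal reading, a well-timed toxicity with no precedent and no better explanation may be left out of the DLT count. If it is still ongoing at Day 42, it may not be followed further, and it may not count as drug-related toxicity at Day 30.

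The effect on the stop ranges from none (no such toxicity, or investigators who classify it as related) to complete (all of it such toxicity, read literally). In the intermediate case of half, the chance that the rule fires falls from 0.564 to 0.225 at an assumed rate of 20%, and from 0.804 to 0.401 at 30%. These figures rest on assumed rates, an assumed share and independent patients. They illustrate how sensitive a threshold of two is and do not estimate what will happen. The defect itself rests on the wording alone.

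**What to change.** Amend 9.4.2 in three respects:

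1. Remove class precedent as a necessary condition for Related. It may stay as supporting evidence.
2. Make the categories exhaustive: an event that does not meet Not Related is classified as related.
3. State that 'related' in 10.2 has the meaning given in 9.4.2.

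The DLT grades and the two-patient threshold stay as written; only the classification feeding them changes. The follow-up rule in 9.1.1 and the Day 30 condition in 5.1 and 7.3 then draw on the same definition without being reworded.

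The cost is a short amendment. The downside is that a few disease-related events may be counted as related, which could make the stop slightly more likely to fire.

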## 10. PATIENT WITHDRAWAL

### 10.1      *CRITERIA FOR PATIENT WITHDRAWAL*

Patients may withdraw their consent to participate in the study at any time without prejudice to his/her future medical care by the physician or at the institution.

If a patient withdraws consent, the date and reason for consent withdrawal should be documented. Patient data will be included in the analysis up to the date of the consent withdrawal.

Wherever possible, the tests and evaluations listed for the final visit should be carried out. The sponsor should be notified of all study withdrawals in a timely manner.

Patients may be removed from the study if any one or more of the following events occur:

- Patient withdrawal of consent
- Dose limiting toxicity
- Discretion of Principal Investigator (reason to be documented on CRF)
- Patient becomes pregnant or begins breast-feeding
- Patient lost to follow-up (defined as the inability to contact the patient on two separate occasions over a period of 1 week)
- Administrative reasons (e.g., the patient is transferred to hospice care)
- An adverse event, which in the opinion of the Investigator, precludes further study participation or fulfills the protocol requirements for withdrawal (e.g., the development of dose limiting toxicity)
- Patient develops an intercurrent illness that precludes further participation, or requires a prohibited concomitant treatment

### *10.2 DOSE LIMITING CRITERIA*

In general, Dose Limiting Toxicities (DLTs) will be considered as toxicities that are related to treatment with I-131-CLR1404 and that are:

1. Hematological
  - a. Any CTCAE Grade 4 toxicity (except Grade 4 neutropenia without concurrent fever which must be present for  $\geq 7$  days to constitute a DLT)
  - b. CTCAE Grade 3 neutropenia with fever
  - c. CTCAE Grade 3 thrombocytopenia associated with bleeding
2. Non-Hematological
  - a. Any CTCAE Grade 3 toxicity despite adequate supportive care (supportive care limited to nausea, vomiting and diarrhea only)
  - b. Any CTCAE Grade 4 toxicity

If 2 patients experience a DLT, study enrollment will be stopped pending discussions with the Principal Investigator, Collectar Medical Monitor and the Agency.

### *10.3 STUDY DISCONTINUATION*

The Sponsor reserves the right to discontinue the study at any time. The Principal Investigator will be compensated for reasonable expenses incurred if it is necessary to terminate the study. Collectar will not compensate the Principal Investigator for evaluation of cases in which the procedures and evaluations were conducted in a manner other than that specified in the protocol. Reasons for early study discontinuation may include, but are not limited to,

- Unacceptable toxicity of study drug
- Request to discontinue the study from a regulatory authority

- Protocol violations
- Poor enrollment
- Company business decision
- Difficulties in manufacturing the investigational product.

#### *10.4 REPORTING AND FOLLOW-UP OF PREGNANCY*

Collectar's Medical Monitor must be immediately informed about any patients who become pregnant while on study. Pregnancies occurring up to 90 days after the completion of the study medication must also be reported to Collectar.

The Investigator should inform the patient of the risks (if any) of continuing with the pregnancy and the possible effects on the fetus. Collectar may recommend monitoring the pregnancy until its' conclusion.

Pregnancy occurring in the partner of a male patient participating in the study should also be reported to Collectar. The partner should also be informed of the risks of continuing with the pregnancy, the possible effects on the fetus (if any), and recommendations for monitoring until conclusion of the pregnancy, if applicable.

### **11. DATA ANALYSIS**

#### *11.1 CASE REPORT FORMS*

All data required by the study will be entered onto case report forms supplied by Collectar. Only those clinical site staff so authorized may enter data onto the case report forms. All entries must be legible and made in black ink pen. If an entry error is made, a single line will be placed through the incorrect entry. The correct entry will then be made, with the correction dated and initialed by the person making the entry. Any corrections to data entered into the CRF must be made in such a way that the original entry is not obscured.

#### *11.2 DATA QUALITY ASSURANCE*

Case report forms will be checked for correctness against source document data by Collectar's monitors. If any entries on the CRFs are incorrect, incomplete or illegible, the monitor will ask the Investigator or the study clinical site staff to make appropriate corrections. Once the CRF page is complete, it will be delivered to Collectar for entry into an electronic database. Prior to this, the completed CRF will again be reviewed for completeness, consistency and legibility. Any discrepancies will be noted on a data clarification form (DCF) which will be sent to the clinical site. The discrepancy will be clarified on the DCF, which will then be returned to Collectar's data entry center.

#### *11.3 SAMPLE SIZE*

As there is little information on the effect of I-131-CLR1404, this study is meant to be hypothesis generating and no formal sample size calculation will be performed.

#### *11.4 DOSIMETRY CALCULATION*

Biodistribution data will be analyzed using the OLINDA methodology to produce time/activity curves and generate organ specific radiation absorbed doses from a 10 mCi injection of I-131-CLR1404. This data, along with blood sampling drawn at specific time points post injection and total urine collection for up to 14 days, will be used to extrapolate and predict organ specific and total body radiation absorbed doses from therapeutic injections of I-131CLR1404. Dosimetry calculations will be instrumental in characterizing the dose escalation schema for subsequent Phase 1/2 protocols.

#### *11.5 STATISTICAL ANALYSIS*

All baseline patient characteristics will be summarized in a tabular format.

Safety data will be described for all patients receiving an infusion of I-131-CLR1404. Safety data will include values for hematology, serum chemistry, urinalysis and vital signs, results of ECG determinations and adverse events. The proportion of patients experiencing adverse events will be reported and SAEs will be summarized.

The I-131-CLR1404 plasma concentration-time data will be determined for each patient. The following PK parameters will be determined:

$C_{\max}$   
AUC (0-144hr)  
Plasma half-life ( $t_{1/2}$ )  
Plasma clearance (Cl)  
Vd

## **12. ADMINISTRATIVE PROCEDURES**

### *12.1 PATIENT INFORMED CONSENT*

No study related procedures will be performed until a patient or their legal representative has given written informed consent to participate in the study. Collectar will provide to the Investigator a sample informed consent form (ICF) that conforms to all the requirements for informed consent according to the International Conference on Harmonization Guidance on Good Clinical Practice (ICH GCP) and US FDA guidelines (21 CFR 50). However, it is up to the Investigator to provide a final ICF that may include additional elements required by the Investigator's institution or local regulatory authorities. The Institutional Review Board (IRB) for each clinical site must approve the ICF prior to study activation; changes to the ICF during the course of the study may also require IRB approval. The ICF must clearly describe the potential risks and benefits of the study, and each prospective participant must be given adequate

time to discuss the study with the Investigator or clinical site staff and to decide whether or not to participate. Each patient who agrees to participate in the study and who signs the ICF will be given a copy of the signed, dated, and witnessed document. A second copy of the signed, dated, and witnessed ICF will be retained by the Investigator in the study files.

## *12.2 ETHICAL CONDUCT OF THE STUDY AND IRB APPROVAL*

The study will be conducted according to the principles of the 2000 version of the Declaration of Helsinki (Appendix B), ICH GCP, and the requirements of all local regulatory authorities regarding the conduct of clinical studies and the protection of human patients.

The Investigator will submit the protocol, the Investigator's Brochure, the ICF and any other material used to inform patients about the study to the local IRB for approval prior to enrolling any patient into the study. The IRB should be duly constituted as outlined in 21 CFR 50. Approval must be in the form of a letter signed by the Chairperson of the IRB or the Chairperson's designee, must be on IRB stationery and must include the protocol by name and/or designated number. If an Investigator is a member of the IRB, the approval letter must stipulate that the Investigator did not participate in the final vote, although the Investigator may participate in the discussion of the study. The Investigator will also inform the IRB of any serious adverse events that the Sponsor reports to regulatory authorities and will provide to the IRB a final summary of the results of the study at the conclusion of the study.

Any amendments to the protocol, other than administrative changes, will be submitted to the IRB for review and written approval will be received before implementation. Such written approval will be forwarded to Collectar by the Investigator.

## *12.3 PROTOCOL AMENDMENTS*

The protocol will only be modified by Collectar. Changes to the protocol must be in the form of a written amendment; changes other than those of a simple administrative nature (e.g., a new telephone number for a Medical Monitor) must be submitted by the Investigator to the local IRB and such amendments will only be implemented after written approval of the requisite IRB. All amendments will also be submitted to local regulatory authorities by Collectar as required by local regulation.

Protocol changes to eliminate an immediate hazard to a study patient may be implemented by the Investigator immediately. The Investigator must then immediately inform the IRB and Collectar who will immediately notify local regulatory authorities.

If an amendment substantially alters the study design or increases the potential risk to the patient, the ICF must be revised and submitted to the IRB for review and approval. The revised ICF must be used to obtain consent from patients currently enrolled in the study if they are affected by the amendment, and the new ICF must be used to obtain consent from new patients prior to enrollment.

